
#### Plans to promote participant retention and complete follow-up {18b}

Efforts to promote participant adherence, as described above, are also expected to increase participant retention. In addition, study staff are available for the duration of the study to identify and respond to barriers to continued participation. The Western dietary pattern intervention period (4 weeks) is considered adequate for the participants to return to baseline in terms of the metabolic health status, as demonstrated by multiple cross-over studies [35]. Despite the 16-week study duration, our team has reported excellent adherence and retention in fully controlled feeding interventions (e.g., DASH and MED studies described above) of similar length, and therefore we are confident individuals will complete the study with minimal dropout or nonadherence [16, 36].

#### Data management {19}

All data, including consent documentation, forms for in-person assessments (e.g., vitals, blood pressure, height, weight), and questionnaires are collected by study staff or self-reported by participants using REDCap and identified by each participant’s unique alphanumeric study ID. REDCap is a secure, web-based application designed to support data capture for research studies and hosted at the University of Colorado, providing (1) an intuitive interface for validated data entry, (2) audit trails for tracking data manipulation and export procedures, (3) automated export procedures for seamless data downloads to common statistical packages, and (4) procedures for importing data from external sources [21, 22]. Exported data for analysis will include only non-protected health information. Tracking of sample collection information and freezer storage location for biospecimens are managed using the TrackVia automated workflow platform (TrackVia, Denver, CO, USA). Dietary intake data are collected via participant self-report through the ASA24®. Study staff specify a unique numeric identifier for each respondent and download system-generated ASA24® usernames and strong passwords that they provide to respondents so that they may access the application.

#### Confidentiality {27}

We will maximize efforts to ensure confidentiality through the use of unique alphanumeric study IDs. Participants are identified throughout the research database by their study ID. Only the research team has simultaneous knowledge of participant identities, ID numbers, and study-related data for all participants in the study. Records and forms are kept in locked file cabinets in a secured room. Any information stored virtually is housed on a secure server and is only accessible to study key personnel who have the password to gain entrance into the REDCap, ASA24®, or TrackVia databases. All computer systems are password-protected against intrusion, and all network-based electronic communications of confidential information are encrypted. Information sent for analysis will not contain any identifiers and will be transmitted in a secure manner. Only study team members who have completed their institutional or the NIH human participants training are able to work on this project.

#### Plans for collection, laboratory evaluation, and storage of biological specimens for genetic or molecular analysis in this trial/future use {33}

As described above, participants will collect urine and stool at home prior to each in-person assessment visit at baseline and intervention weeks 4, 8, 12, and 16 (pre/post each dietary intervention period). In-person assessment visits will consist of fasting blood draws and optional upper GI sampling via EnteroTracker®. All biospecimens (blood, urine, stool) will be processed and stored at – 80 °C for batch analyses of primary and secondary outcomes upon study completion as well as unspecified future analyses to learn more about heart disease, inflammation, and gut health or other health problems.

## Statistical methods

### Statistical methods for primary and secondary outcomes {20a}

Assessment of the primary outcome of change in FSCs will be completed using the intercept of linear mixed effects models (LMMs) with change in FSCs (post–pre) as the outcome and a random intercept to control for repeated measures. Analysis will be stratified by mini-MED and Western interventions since we expect FSCs to increase during the mini-MED arm and to decrease during the Western arm. FSCs that significantly increase during the mini-MED interventions and significantly decrease during the Western interventions will be considered validated. We will adjust for multiple testing using false discovery rate (FDR) for the number of FSCs [37]. We will complete stratified analysis by intervention period to assess reproducibility of FSCs in increase (mini-MED) and decrease (Western). The relationship between cardiometabolic health indicators and diet intervention will be assessed using LMMs similar to that described above. The relationship between cardiometabolic health indicators and FSCs will be assessed using LMMs over all intervention periods with an interaction term for FSCs and diet (i.e., mini-MED, Western) to capture differential effects by diet.

Data for exploratory outcomes related to the gut microbiota will be evaluated to assess (1) change over dietary intervention, (2) association with cardiometabolic health indicators, and (3) descriptive differences between upper GI and stool microbiota. Data will be presented as sequence count data. For both 16S rRNA gene amplicon and metagenomic datasets, taxa or genes that differ in abundance or prevalence between intervention groups and pre- to post-intervention will be identified by negative binomial mixed effects regression, with the total sequence count for each subject as a covariate [38]. Similarly, associations between gut microbiota variables and continuous cardiometabolic health indicator variables will be assessed using LMMs controlling for total sequence count. Permutation-based analysis of variance (PERMANOVA) tests using common beta-diversity indices (e.g., UniFrac, Bray–Curtis) will assess between-group differences in overall microbial community structures. Exploratory analyses of gut microbiota data also will be performed using unsupervised ordination methods (e.g., principal coordinates analysis). Supervised classification methods (e.g., random forests) will be used to build models of cardiometabolic health indicators, with the goal of identifying particular microbial taxa, or host factors, that best predict the cardiometabolic health indicators. To control for multiple testing for FSCs, cardiometabolic health indicators, and microbial taxa/genes, we will use an FDR correction [37].

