**Methods:**

Individuals with overweight/obesity who do not habitually consume a MED dietary pattern will complete a 16-week randomized, multi-intervention, semi-controlled feeding study of isocaloric dietary interventions: (1) MED-amplified dietary pattern, containing 500 kcal/day from eight MED target foods: avocado, basil, cherry, chickpea, oat, red bell pepper, walnut, and a protein source (alternating between salmon or unprocessed, lean beef), and (2) habitual/Western dietary pattern, containing 500 kcal/day from six non-MED target foods: cheesecake, chocolate frozen yogurt, refined grain bread, sour cream, white potato, and unprocessed, lean beef. After a 2-week washout, participants complete four, 4-week intervention periods, with biospecimen sampling and outcome assessments at baseline and at intervention weeks 4, 8, 12, and 16. The primary outcome is change in the relative abundance of FSCs from the eight MED target foods in participant biospecimens from baseline to the end of each intervention period. Secondary outcomes include mean change in cardiometabolic health indicators, inflammatory markers, and adipokines. Exploratory outcomes include change in diversity and community composition of the gut microbiota.

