### Trial design {8}

This trial is a 16-week randomized, multi-intervention, semi-controlled feeding study of Mediterranean-amplified (mini-MED) and habitual/Western-style (Western) isocaloric dietary interventions containing 500 kcal/day from target foods. Participants are randomized (1:1) to start either the mini-MED or the Western dietary intervention, with subsequent assignment to the other upon completion of the first. Each 4-week intervention (mini-MED and Western) is repeated once. The Western intervention serves as both a washout of the mini-MED foods and a negative control for the postprandial response when the mini-MED foods are not consumed. Within the mini-MED arm, participants are further randomized to first receive salmon (mini-MED salmon) or lean, unprocessed beef (mini-MED beef) as a protein source, with consumption of the alternate protein source in their second mini-MED intervention period (Fig. 1). Outcome measures and biospecimen sampling take place at baseline and intervention weeks 4, 8, 12, and 16, and outcomes will be assessed using an exploratory approach.

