### Outcomes {12}

The primary outcome for this clinical trial is change in the relative abundance of FSCs from beginning to the end of each dietary intervention period in participant plasma samples. Secondary outcomes include detection of FSCs in participant urine samples as well as mean changes in cardiometabolic health indicators (e.g., total cholesterol, LDL cholesterol, HDL cholesterol, triglycerides, insulin, glucose, systolic and diastolic blood pressure), inflammatory markers (e.g., C-reactive protein, interleukin-6, tumor necrosis factor-alpha, alpha-1-acid glycoprotein), and adipokines (e.g., leptin, adiponectin) over each dietary intervention. Exploratory outcomes include changes in diversity and community composition of the gut microbiota over each dietary intervention period.

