### Methods in analysis to handle protocol non-adherence and any statistical methods to handle missing data {20c}

Data from all randomized participants will be analyzed using intention-to-treat. Compounds with more than 90% missing over all plasma or urine samples will be removed. Remaining compound values will be log2 transformed, and data will be corrected for batch and order effects using residuals from linear regression with FSC abundance as the outcome with order, batch, and order by batch interactions as predictors after removing outliers and values below the detection limit (i.e., missing). Outliers will be defined as having residuals from the model that are more than the third quartile plus 1.5*interquartile range or less than the first quartile minus 1.5*interquartile range. The resulting linear model will be used to predict compound values for all observations (i.e., including outliers). After batch and order correction, QC values will be shifted by the minimum observed value for each compound, and compounds with a high coefficient of variation (CV ≥ 0.3) for QC values will be removed. Given the expectation of meaningful and real zero values (i.e., in baseline plasma samples) and arbitrary quantities of untargeted metabolomics, adjusted values will be ranked within each compound to enable parsimonious inclusion of zero values. Missing values will be given the lowest ranks. In case of multiple missing values or duplicate normalized values, an average of ranks will be assigned.

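### The Western-decrease test pools Western-first participants' first period, which starts from a washed-out baseline where little or no decrease is expected, so a leg that validation depends on is diluted

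*Protocol article*

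**What the plan says.** Trial design {8} fixes the allocation: "Participants are randomized (1:1) to start either the mini-MED or the Western dietary intervention". Each diet is given twice in alternation, so the two diet orders are W-M-W-M and M-W-M-W (M = mini-MED, W = Western). Section {11a} places a 2-week washout before period 1 only. Section {8} describes the Western diet as both a washout of the mini-MED foods and a negative control.

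The primary analysis in {20a} is the intercept of "linear mixed effects models (LMMs) with change in FSCs (post–pre) as the outcome and a random intercept to control for repeated measures", run separately for mini-MED and Western, "since we expect FSCs to increase during the mini-MED arm and to decrease during the Western arm". The decision rule is: "FSCs that significantly increase during the mini-MED interventions and significantly decrease during the Western interventions will be considered validated". Reproducibility is then examined: "We will complete stratified analysis by intervention period to assess reproducibility of FSCs in increase (mini-MED) and decrease (Western".

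On the level at the start of the trial, {20c} motivates its ranking step with: "Given the expectation of meaningful and real zero values (i.e., in baseline plasma samples".

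The outcome is defined in two ways. Outcomes {12} measures change "from beginning to the end of each dietary intervention period in participant plasma samples"; the abstract measures it "from baseline to the end of each intervention period".

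**The concern.** A fall can be expected only where there was something to fall from. A Western period that follows mini-MED starts at the fed level. Period 1 of a Western-first participant starts after the washout, at a level the plan itself expects often to be zero. The ranking in {20c} sharpens this: a non-detect already holds the lowest (averaged) rank, and if it is still a non-detect at week 4 its change is exactly zero.

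The reason {20a} gives for testing a decrease therefore covers only part of the data in that test. Because validation needs both legs, a diluted Western leg can cause a genuine intake biomarker to be rejected. Reproducibility within individuals is part of the primary hypothesis in {7}, so a fully reproducible FSC could also look irreproducible merely because its first Western stratum is made up wholly or partly of baseline starters.

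**Working it through.** **Plan's own power figure.** Section {14} claims 80% power for a paired t-test with N = 20, d = 0.45 and alpha = 0.05/21 = 0.0024. The noncentral t distribution gives 0.10 two-sided (0.16 one-sided), and 0.47 two-sided at d = 0.75. The stated figure does not reproduce. That is a separate matter; here it means only that {14} cannot serve as the benchmark, so power is computed directly.

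**Inputs from the article.** N = 20 completers; 1:1 start; two Western changes per participant; d = 0.45 (smallest) and 0.75 (median) from {14}; alpha = 0.0024 used only as a scale, since {20a} uses FDR and {20c} uses ranks.

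**Assumptions.** A change after mini-MED has mean −d and SD 1. A change from baseline has mean −b·d, where b is the baseline level as a share of the fed level, and SD s. Neither b nor s is in the article. Changes within a person are uncorrelated unless stated.

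**Step 1, share affected.** W-M-W-M: 10 participants, Western in periods 1 (from baseline) and 3. M-W-M-W: 10 participants, Western in periods 2 and 4. Baseline starts = 10 of 40 = 25% (11 of 44 if all 22 enrolled are counted).

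**Step 2, expected pooled change.** −d × (b + 1 + 1 + 1)/4.
- b = 0: 0.75d.
- b = 0.5: 0.875d.

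**Step 3, period-stratified check.** The article does not define the strata.
- *Calendar periods.* Western in period 1 (n = 10) consists only of baseline starters. With b = 0, a significant decrease occurs by chance alone: 2.5% at two-sided 0.05. Periods 2, 3 and 4 are unaffected.
- *First versus second Western repeat.* With b = 0 the first-repeat mean is (10 × 0 + 10 × d)/20 = 0.5d. At d = 0.75 and p < 0.05, simulated power in the first repeat is 0.31 (s = 1) to 0.52 (s = 0.2), against 0.89 in the second.

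**Step 4, power of the pooled decrease leg.** Simulation, two-sided, d = 0.75, p < 0.0024. As written: t-test on each participant's mean Western change, which equals the intercept test with balanced data. Restricted: the 30 changes that follow mini-MED, tested with 19 to 29 degrees of freedom.

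| b | s | As written | Restricted |
|---|---|---|---|
| 0 | 1 | 0.49 | 0.72–0.77 |
| 0 | 0.5 | 0.62 | 0.72–0.77 |
| 0 | 0.2 | 0.66 | 0.72–0.77 |
| 0.5 | 1 | 0.72 | 0.72–0.77 |
| 0.5 | 0.2 | 0.87 | 0.72–0.78 |

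With within-person correlation 0.3, b = 0 and s = 1, the pair is 0.35 versus 0.61. At d = 0.45, b = 0 and s = 1, it is 0.12 versus 0.18–0.22. At p < 0.05, d = 0.75, b = 0 and s = 1, it is 0.91 versus about 0.98.

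**The case against.** Several stronger readings are tempting, and the article does not support them.

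- *A decrease is impossible in Western-first period 1.* Section {20c} expects zeros in baseline plasma but does not say every FSC is zero in everyone. Eligibility requires only a Mediterranean score of 7 or less out of 14, so some habitual intake of target foods is allowed, and {11a} does not say which foods the washout excludes. The text supports little or no expected decrease.
- *The reproducibility check fails by design.* Only the calendar-period-1 stratum is null. Three Western strata are sound on that reading, and on the other reading the first stratum is diluted, not null. Calendar stratification would even display the baseline starters as a negative control.
- *The power loss is large.* It is large only if changes from a zero baseline vary as much as real falls (s = 1). Zeros before and after should vary less, and the gap then narrows to 0.66 versus 0.72–0.77. If baseline sits at half the fed level, restriction gains little or loses power.
- *Under the abstract, no Western period could show a fall.* The abstract's wording would imply this, but {12}, {18a} and the post-minus-pre outcome in {20a} fix the start of each period as the reference. The abstract is loose wording.

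It is also fair to say that {8} calls the assessment exploratory, and that the mini-MED leg is untouched because both orders enter mini-MED from a low level. What remains is that the validation rule requires a decrease over a pool, a quarter of which the plan gives no reason to expect to fall.

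**Conclusion.** The point holds as a should-fix. As written, {20a} dilutes a leg on which validation depends: 25% of Western changes start from the washed-out baseline, and the pooled estimate is about 75% of the true post-mini-MED decrease if baseline FSCs are near zero, or 87.5% if they sit at half the fed level. The dilution of the estimate and the weak first Western stratum follow from the design and the plan's own expectation of zeros. The size of the pooled power loss is not established, because it turns on baseline level and variability that the article does not give. The bias runs one way: true biomarkers can be missed, but none is falsely validated by it. The arithmetic applies to foods supplied in both mini-MED periods. Salmon and beef alternate, and beef is also in the Western diet, so their expected changes differ.

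**What to change.** In {20a}, define the decrease leg, both pooled and by period, on Western periods that directly follow a mini-MED period, and state what the period strata are. Report period 1 of the Western-first participants separately as a negative control, with estimate and confidence interval and little or no change expected; {8} already gives the Western diet that role. Keep the all-Western analysis as a sensitivity analysis. As a minor edit, align the abstract with {12}, so that change runs from the start of each period.

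The cost is wording only, with no change to conduct or sampling. The downside is that 25% of Western changes leave the decrease test, which can cost some power for FSCs with appreciable baseline levels. The choice should be fixed before results are seen: {33} defers sample analysis to study completion and {21b} plans no interim look, so making it afterwards would be post hoc.

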#### Sample size {14}

Most of our planned analyses use each individual as their own control by looking at the change over each dietary intervention period. This reduces between subject variability compared to a cross-sectional analysis and increases the statistical power at a given sample size. To obtain a reasonable minimum expected effect size for the mean difference divided by the standard deviation of the difference (i.e., Cohen’s *d* effect size), we used our analysis of salmon FSCs [13]. The minimum salmon FSC effect size that passed an FDR adjustment was 0.45. Using a paired *t*-test after consuming the food, a sample size of *N* = 20 was needed to achieve 80% power for this effect size of 0.45 and a Bonferroni multiple testing adjustment for the number of compounds that increased in the preliminary MED data (*N*_compounds_ = 21; *p*-value_adjusted_ = 0.05/21 = 0.0024). We assume a 10% loss to follow-up based on our experience in similar dietary intervention trials and therefore enroll *n* = 22 eligible individuals to have *n* = 20 individuals complete the trial.

We also evaluated the power of *N* = 20 sample size further using the Bonferroni adjustment for the 21 compounds that increased after consumption of the preliminary Mediterranean diet foods (*p*_adj_ = 0.0024) and a stricter adjustment using all 355 compounds that were detected in the MED foods and plasma (*p*_adj_ = 0.05/355 = 0.00014). For both significance thresholds, we achieve power across a range of relevant effect sizes (Fig. 2) including nearly 100% power to detect an effect size of 0.75 (the median effect size for the salmon FSCs that passed the FDR threshold).

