**Fig. 2 Fig2:**
[figure not shown]
Power calculation for mini-MED clinical trial. Power (*y*-axis) for *N* = 20 for a paired *t*-test of the difference between post- and pre-consumption of a food. Power was evaluated over various effect sizes (*x*-axis, mean difference/SD of difference) for three significance thresholds: nominal threshold of 0.05 (yellow), Bonferroni corrected threshold for 21 compounds that increased after consumption in the initial study (*p* = 2.4e − 3), and Bonferroni corrected threshold for 355 compounds that were detected in MED foods and plasma (*p* = 1.4e − 4)

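### The stated power is for a single before-after test, but an FSC counts as validated only if two such tests are both significant, in opposite directions

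*Protocol article*

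**What the plan says.** Under Statistical methods for primary and secondary outcomes {20a}, the primary outcome is tested "using the intercept of linear mixed effects models (LMMs) with change in FSCs (post–pre) as the outcome and a random intercept". One model is fitted per diet: "Analysis will be stratified by mini-MED and Western interventions". The decision rule is explicit: "FSCs that significantly increase during the mini-MED interventions and significantly decrease during the Western interventions will be considered validated". Multiplicity is handled by FDR: "We will adjust for multiple testing using false discovery rate (FDR) for the number of FSCs".

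Sample size {14} rests on a different test: "Using a paired *t*-test after consuming the food", with effect size 0.45 (mean difference over SD of the difference), N = 20, 80% power and a Bonferroni threshold of 0.05/21 = 0.0024. It adds a stricter threshold, 0.05/355 = 0.00014, and claims nearly 100% power at effect size 0.75 for both thresholds. The Fig. 2 legend confirms that what is plotted is a paired t-test "of the difference between post- and pre-consumption of a food".

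Two design facts matter. Each diet is given twice, in alternation, from a randomised starting diet (Trial design {8}). Samples at weeks 4, 8 and 12 close one period and open the next (Plans for assessment and collection of outcomes {18a}).

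**The concern.** The rule needs two significant results per compound, a rise on mini-MED and a fall on Western. Power is given for one result only. Neither the Western decrease nor the joint requirement is powered anywhere.

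The decrease is the weaker test. Participants who start on Western enter it straight from the washout baseline. If they have not been eating the target foods, their first Western period has little to clear, which dilutes the average fall.

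The cost is missed biomarkers. A reader who trusts the stated power would take failure to validate as good evidence that a compound is not a biomarker. At the power the rule actually has, failure would often be the expected result for a real one.

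**Working it through.** **Plan's own figure first.** For a two-sided paired t-test, the noncentrality is d√N on N − 1 degrees of freedom. With N = 20, √20 = 4.472, and the critical value at 0.05/21 on 19 df is 3.503.

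- d = 0.45: 0.45 × 4.472 = 2.012, power 10.4% (stated: 80%). Reaching 80% needs N = 79.
- d = 0.75: 0.75 × 4.472 = 3.354, power 46.6% (stated: nearly 100%). At 0.05/355 it is 14.5%.
- One-sided testing does not rescue it: 15.5% at d = 0.45.

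Entering 80 pairs gives 80.8% at d = 0.45, and 99.97% and 99.5% at d = 0.75. That would fit 20 participants × 4 periods counted as independent pairs, but this is an inference; the protocol does not say so.

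**Power of the rule.** Inputs: 20 completers, 10 per starting diet, five visits, and d as the effect on a single-period change whose SD is set to 1. Assumptions not in the protocol: unfed baseline, no drift or carryover, equal response in everyone, independent visit errors, normal data. Each within-diet mixed-model intercept, with two balanced changes per person, is replaced by a t-test on participant means (19 df).

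*Increase test.* The mean of two changes has variance 1/2, so the noncentrality is d√40. At d = 0.75 this is 0.75 × 6.325 = 4.74, giving about 87%. At d = 0.45 it is 2.85, giving 29.6%.

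*Decrease test.* Mini-MED-first participants fall by d on average. Western-first participants fall by d/2, since their first Western change is zero. The overall mean is 0.75d, and the variance is about 0.5 + (20/19)(d/4)².

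- d = 0.75: mean 0.5625, variance 0.537, SD 0.733; noncentrality 0.5625 × 4.472 / 0.733 = 3.43, about 49%.
- d = 0.45: mean 0.3375, variance 0.513, SD 0.716; noncentrality 2.11, about 11%.

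*Both together.* The two tests share samples, so joint power comes from simulation (at least 20,000 trials per setting):

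| d | threshold | single paired test, N = 20 | increase | decrease | both (the rule) |
|---|---|---|---|---|---|
| 0.45 | 0.05/21 | 10.4% | 30% | 11% | 9% |
| 0.75 | 0.05/21 | 46.6% | 87% | 49% | 48% |
| 0.75 | 0.05/355 | 14.5% | 52% | 16% | 14% |
| 0.45 | 0.05 | 48.0% | 77% | 51% | 49% |
| 0.75 | 0.05 | 88.9% | 99% | 91% | about 90% |

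The analysis uses FDR, whose effective threshold is not known in advance. The rows are therefore a range, not a forecast.

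**Sensitivity at 0.05/21.**

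- If half of the change variance is person-to-person response, the rule falls to about 41% (d = 0.75) and 7% (d = 0.45).
- Dropping the Western-first first period from the decrease test raises d = 0.75 to about 62%.
- Across response variation and an unfed or half-fed baseline, the rule ranges from about 38% to 61% at d = 0.75 and from 6.7% to 11.3% at d = 0.45.

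**The case against.** The strongest defence is that the second test is deliberate. Background and rationale {6a} states the premise that FSCs will not be found when the food is not eaten, and Trial design {8} makes Western the washout and negative control. Requiring a demonstrated fall follows from that, and it makes the rule conservative. This stands: the rule is not the error, its stated power is.

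It can also be said that nearly all of the shortfall from 80% comes from the single-test arithmetic. That stands too. The rule's power lies close to the correctly computed single test in every row above, because averaging two periods per diet gains about what the second test costs. The agreement depends on the assumptions, though: 62% against 46.6% once the Western-first first period is dropped. Correcting the arithmetic alone would still describe a different test.

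A reader might infer four stronger things that the documents do not support.

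- *The diets are never compared.* No diet contrast is tested for the primary outcome. But every mini-MED change except the first in mini-MED-first participants starts from an end-of-Western sample in the same person, so the increase test is already close to a contrast.
- *The rule halves power in general.* Against a fed-versus-unfed contrast of end-of-period levels, the ratio of powers is 0.91 to 0.96 at d = 0.75 and nominal 0.05. It is 0.55 to 0.83 at 0.05/21 and 0.27 to 0.64 at 0.05/355. Part of the loss comes from the Western-first first period.
- *One visit-level contrast should replace the rule.* Take a compound that steps up by β in each mini-MED period and never clears. The difference between starting-diet groups over the five visits is β × (0, 1, 0, 1, 0), and the difference in fed status is (0, 1, −1, 1, −1). The fed coefficient is (1 + 1)/4 = β/2, not zero. At d = 0.75, that contrast plus checks on the signs of the two changes would validate such a compound in 48% of trials at 0.05 and 21% at 0.05/21; the rule does so in 2.5% and 0.2%. Without a participant-level random fed effect, the contrast also rejects upward in 5.4% of trials instead of 2.5% when response varies but its mean is zero.
- *Shared samples or drift make the rule unsafe.* With no effect, both tests pass together in 0.8% to 1.0% of trials at 0.05, which is low, and the plan never claims that they are independent. Drift by visit is an assumption: samples are batch-analysed at study completion and corrected for batch and order.

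**Conclusion.** The point holds as a mismatch between the decision rule and the power statement. The protocol fixes a two-test rule and reports power for one test, so neither 80% nor nearly 100% applies to validating a compound. Under the assumptions listed, the rule has about 9% and 48% power at the protocol's two effect sizes at 0.05/21, and about 14% at 0.75 and 0.05/355. Only near nominal 0.05, and at the larger effect size, is it comfortable (about 90%).

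These figures are for compounds of foods fed in both mini-MED periods and not in Western; salmon and beef FSCs have different feeding patterns and were not computed. The plan analyses ranks whereas the calculation uses normal data, so the figures are approximate. The conclusion that the stated power is not delivered does not depend on the exact values. The single-test arithmetic in Sample size {14} is a separate error and should be corrected in its own right.

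**What to change.** In Sample size {14} and Fig. 2, restate power for the rule that will be applied: both tests, in the stated directions, at the planned multiplicity threshold. Show the increase test, the decrease test and the joint result separately, and state what is assumed about baseline exposure, variation in response and the Western-first first period.

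Keep the two-test rule as the validation criterion. If wanted, add a supportive analysis: a mixed model of visit-level FSC values with a visit term, a fed indicator and a participant-level random fed effect, reported as an estimate with its interval.

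The cost is one simulation and revised wording, with no new samples or visits. The honest power will be much lower than stated, so non-validated compounds will have to be reported as inconclusive rather than refuted.
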